## Training to deliver the PFMT intervention

Training will be delivered after Round 2 data collection has been completed. Clinicians who have been identified locally through the service planning process will undergo one full day of bespoke training to prepare them for delivering PFMT to women with POP recruited to the study. This training has been developed specifically for this study in partnership with the Pelvic, Obstetric and Gynaecological Physiotherapy (POGP) Group. The training will be delivered by two POGP trainers per full day session and one member of the research team. It includes training in PROPEL specific research processes and paperwork, an introduction to internal examination, and delivery of the PFMT programme for women. This training will ensure that they meet minimum levels of competencies developed in agreement with the POGP. There will also be ongoing support available locally for staff who have received this training from specialist women’s health physiotherapists, including observation of initial assessment and treatment. Any additional support or training required by staff to deliver the PFMT programme for women will be recorded (Fig. 1).

**Fig. 1 Fig1:**
[figure not shown]
PROPEL Realist Evaluation and outcomes study flowchart EQ-5D-5 L: EuroQol 5 dimensions questionnaire; ICIQ-UI SF: International Consultation on Incontinence Questionnaire Urinary Incontinence short form; n: number of participants; PFMT: Pelvic floor muscle training; POP: Pelvic organ prolapse

## Data collection

### A) Realist Evaluation

Qualitative data for the RE will be collected in four rounds at different time-points over an 18 month implementation period across each site to understand local contexts and decisions regarding delivery of PFMT for prolapse and to monitor implementation, up-take, adherence and impact. **Error! Reference source not found.** Summarises data to be collected during each round. Two rounds of data collection will take place during the planning stages (what to implement and how, and local theories of change), one round during implementation/delivery of the models (how is it working) and one round immediately post implementation (reflection on how it has worked). All focus groups, interviews and service planning meetings will be recorded and transcribed.

### B) Outcomes study

It is anticipated that each staff member in the five sites will recruit five women to take part in the study and who will: agree to complete study outcome questionnaires, have the POP-Q assessment (pre- and 6 months post) and take part in qualitative interviews if requested. Patient outcomes as used in the POPPY trial will be collected at baseline (immediately prior to first (assessment) appointment) and at six months and one year follow-up; clinicians will collect POP-Q data at baseline and 6 months during specified appointments and the remaining measures (POP-SS, EQ-5D-5 L, ICIQ-UI SF and patient demographic data all collated within patient completed questionnaire) will be collected by post at each time point.

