### B) Outcomes study

Outcomes data will be collected before and after women receive the PFMT intervention in each location/model of service delivery to establish whether the improvements observed in the POPPY trial are also observed under different models of delivery and in non-trial real world NHS settings (see Table 2).

**Table 2 Tab2:** Outcomes Study site descriptions

Site	Urban/rural	POPPY experience	Current dominant model
1	Urban	POPPY recruiting centre	Primary and secondary care provision of specialist physiotherapy referred by primary care and acute services with a mix of 1:1 and group provision available. Women not routinely sent to physiotherapy as first line treatment. Several POPPY physiotherapists providing current input to women with POP
2	Urban	Large involvement in medically driven trials but no focus on physiotherapy based trials	Currently has some specialist physiotherapy involvement but greater specialist nurse-led service for women
		No POPPY involvement	
3	Rural	No POPPY involvement and limited other trial involvement	Current interest in re-design and expanding to junior grade physiotherapists and other nursing staff (as practitioners with special interest)
4	Urban	No POPPY involvement	Currently has some specialist physiotherapy involvement, looking to increase capacity for PFMT provision with other staff groups
5	Urban	No POPPY involvement	Currently has some specialist physiotherapy involvement, looking to increase capacity for PFMT provision with other staff groups

*PFMT* Pelvic Floor Muscle Training, *POP* Pelvic Organ Prolapse, *POPPY* Pelvic Organ Prolapse PhysiotherapY trial

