### Recruitment/sampling

Women who are awaiting treatment for prolapse at study sites will be potential recruits if they are eligible and provide written, informed consent to take part. We aim to recruit 120 women to the outcomes study.

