### Inclusion criteria

Women 18 years of age or above, presenting with symptomatic stage I, II or III prolapse of any type who are suitable to be referred for PFMT and who are willing to take part in the research and comply with necessary data collection.

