### B) Outcomes data

Descriptive statistics will be tabulated for all outcomes at each time point, showing means and SDs for POP − SS and EQ − 5D-5 L, proportions for POP − Q, the need for further treatment, and frequencies for the number of NHS contacts. Differences (and correlations where appropriate) between baseline and 6 − months and between baseline and 12 − months will be calculated. We will initially examine the differences before and after intervention using paired t-tests and chi-square tests. We will fit appropriate generalised linear models on the difference between outcomes before and after intervention, adjusting for baseline measurements and potential confounders (e.g. demographic factors, study site). If possible, we will also explore the effect of different levels of adherence to PFMT using structural mean models [28]. Complete case analyses will be performed throughout, with missing data being addressed in secondary analyses using multiple imputation methods.

POP − SS and EQ − 5D 5L will be treated as continuous data, POP − Q as ordinal, NHS contacts as count data and the need for further treatment (e.g. surgery or pessary) as binary data. In order to facilitate the understanding of prolapse related outcomes, individual items of the POP − SS will also be analysed separately and an additional dichotomous POP − Q measure (above/below the hymen) will be included in the analysis.

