### C) Economic evaluation

Incremental cost-effectiveness ratios (ICERs) will be computed comparing the costs and outcomes of the different modes of delivery. The difference in effectiveness will be expressed in terms of the change in POP-SS Score. These data will be retrieved from the women’s questionnaire responses to the POP-SS outcome measure. The difference in utility will be expressed in terms of QALYs. These data will come from the EQ-5D-5L instrument. Where appropriate the analysis of incremental costs, effectiveness and cost-effectiveness will be based on similar statistical models as those already outlined (Table 3).

**Table 3 Tab3:** PROPEL Realist Evaluation data collection process

Data collection method	Participants (per site)	Round 1 - Discussion and development of the models	Round 2 - Operationalising the models for successful implementation	Round 3 - Delivering the models	Round 4 - Review of the models
Focus groups with women	8–10 women living with prolapse who have been through the current service, identified by specialist PTs in the area	To understand initial perceptions of the acceptability of PFMT, preferences for service delivery models, what the service might look like (referrals, location etc.)			
Service planning meeting	Local service managers, clinical leads, consultants and other relevant staff groups identified by the study specialist PTs at each location and invited to attend	(1 meeting/site) Discuss current service provision, local capacity issues and how these might be addressed with the available or an extended staff pool	(1 or 2 meetings/site) Observe the decision making process, firming planning decisions around what to implement and how the service will be operationalised within the current service structure		
Interviews with managers/service leads	2 interviewees selected from key decision makers, likely those attending the SPM	To explore any anticipated barriers or facilitators and explore further contextual detail that may influence choice of service model and implementation	To explore operationalisation of the decision and how this will be translated to staff involved in the project	To understand how referrals are made and cascaded to trained staff, any anxieties voiced about training/support, local resources	To explore the perceptions of the success of the model and sustainability, possible modifications, impact of the study, future plans

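### Recruitment by the clinicians whose delivery is under evaluation leaves room for selection in an uncontrolled before-after study, and the planned adjustment covers only measured case mix

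*Protocol article*

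**What the plan says.** **Who recruits.** Data collection, B) Outcomes study: "It is anticipated that each staff member in the five sites will recruit five women to take part in the study". The target under Recruitment/sampling is "We aim to recruit 120 women to the outcomes study".

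**Who the staff are.** Under Training to deliver the PFMT intervention, locally identified clinicians receive "bespoke training to prepare them for delivering PFMT to women with POP recruited to the study". The same training day covers the study's research procedures and paperwork.

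**Who can be recruited.** "Women who are awaiting treatment for prolapse at study sites will be potential recruits if they are eligible" (Recruitment/sampling). The inclusion criteria add women "who are suitable to be referred for PFMT and who are willing to take part in the research and comply with necessary data collection".

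**How the data are used.** Methods/design, B) Outcomes study: "Outcomes data will be collected before and after women receive the PFMT intervention in each location/model of service delivery". The analysis uses paired tests, then models of the change, "adjusting for baseline measurements and potential confounders (e.g. demographic factors, study site" and similar factors (Data analysis, B) Outcomes data). The study aims in the Background include exploring whether different staff mixes can achieve the clinical outcomes. Under Data analysis, C) Economic evaluation: "Incremental cost-effectiveness ratios (ICERs) will be computed comparing the costs and outcomes of the different modes of delivery", with effectiveness expressed as change in POP-SS.

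**The concern.** The person who delivers the treatment appears also to be the person who decides whom to enrol. Two of the inclusion criteria, suitability for referral and willingness to comply, call for judgement. A newly trained clinician has an understandable reason to begin with women who seem motivated and straightforward.

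In a randomised comparison, selection of this kind would mainly affect generalisability. Here the primary estimate is the change within one cohort, so any selection on expected change enters the estimate itself. Two conclusions are exposed:

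- **The before-after change**, which is meant to show whether the benefit seen in POPPY carries over to ordinary NHS services.
- **The contrasts between staff groups and delivery models**, including the cost-effectiveness ratios, if some groups select more than others.

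Expected motivation or response is not among the adjustment variables named. Selection cannot be undone once the women are enrolled.

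**Working it through.** **1. The recruitment arithmetic.** 120 women / 5 per staff member = 24 recruiting staff. 24 / 5 sites = 4.8 per site. The projection of five each is consistent with the target of 120.

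**2. Inputs for an illustration.**

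- From Sample size: SD of the change in POP-SS = 5.5; minimum clinically important difference = 2; n = 120 pairs.
- Assumed, because the document gives neither: each clinician has m eligible women and enrols the five who look most promising; that impression correlates r with later change.

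The sample-size section's power statement plays no part in this check.

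**3. Formula.** Shift in mean change = (mean of the top 5 of m standard normal scores) × r × 5.5.

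**4. Five of ten.** Mean of the top five = (1.539 + 1.001 + 0.656 + 0.376 + 0.123) / 5 = 3.695 / 5 = 0.739. So shift = 0.739 × 5.5 × r = 4.06 × r.

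| r | Shift (POP-SS points) | Share of the 2-point difference |
|---|---|---|
| 0 | 0 | 0% |
| 0.1 | 0.41 | 20% |
| 0.2 | 0.81 | 41% |
| 0.3 | 1.22 | 61% |

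**5. Dependence on the assumed pool.**

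| Eligible women per clinician | r = 0.1 | r = 0.3 |
|---|---|---|
| 6 | 0.14 | 0.42 |
| 8 | 0.30 | 0.91 |
| 10 | 0.41 | 1.22 |
| 20 | 0.67 | 2.00 |

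With a pool of exactly five there is nothing to select and the shift is 0.

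**6. Comparison with the study's precision.** The 95% confidence half-width for the whole-cohort mean change is 1.96 × 5.5 / √120 = 0.98. At five of ten, r = 0.1 gives a shift of less than half of this, and r = 0.3 gives one that exceeds it.

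**7. Contrast between staff groups.** With the same pool of ten, bias = 4.06 × (r in group A − r in group B). Equal selection gives 0. Correlations of 0.3 and 0.2 give 0.41. Correlations of 0.3 and 0 give 1.22, which is the extreme case within this range.

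**8. What the stated safeguards reach.** Adjustment removes the part of selection that runs through baseline score, demographics and site. POP-SS is self-completed and posted, so the clinician does not score it. That protects the measurement but does not determine who is in the cohort.

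**The case against.** The strongest case on the other side has five parts.

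- **The sentence is a projection.** It states what is anticipated. A reader might infer a fixed quota of women hand-picked from each clinician's own list, with specialists left the harder cases. The document says none of this. Table 3 speaks of referrals being passed on to trained staff, and the exclusion criteria may be applied through the referral source. Both suggest that women may arrive by a pathway. This stands, and the stronger reading is not supported.
- **Timing limits what can be selected on.** Baseline data are collected just before the first assessment appointment, so an impression may have to come from referral information. This stands in part: it lowers the plausible r but does not make it zero.
- **The direction is uncertain.** Women with uncomplicated prolapse may start with lower scores and have less room to improve, which would reduce the change. This stands.
- **An article condenses the full protocol.** An approach rule or screening log may exist there. A reader might also infer that Reach, in the RE-AIM framework, has no denominator. That cannot be concluded from an article. The point rests on what is stated, namely who recruits.
- **The stakes are bounded.** The powered question is the whole-cohort change. The skill-mix aim is exploratory, and delivery models are chosen locally and not randomised, so those contrasts would remain confounded even with consecutive invitation. This stands, but the whole-cohort change is itself exposed.

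The Realist Evaluation's Setting section has the research team taking consent, apparently from participating staff. Even if this covered the women, it would not settle who approaches them.

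**Conclusion.** The point holds as a weakness in a stated design choice. On the natural reading, the evaluated clinicians recruit the women in a study without a concurrent control, and nothing in the article counters the selection this permits. That each clinician treats only the women she or he recruited is an inference and is not needed for the effect on the overall change.

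The document does not show that selection will occur, how large it would be, or which way it would act. The figure of 0 to 1.2 points rests wholly on the assumed pool of ten, top-five selection and a correlation of 0 to 0.3. At the lower end there is no effect. At the upper end it is about 60% of the 2-point difference and larger than the confidence half-width of 0.98. The skill-mix and model comparisons are affected only to the extent that selection differs between staff groups. The change is worth making because the safeguard is cheap and the analysis cannot fully replace it.

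**What to change.** Amend Data collection, B) Outcomes study so that, from a set date, eligible women awaiting treatment are invited in waiting-list order, for example with the appointment letter, until each clinician has five consenting women. Keep a short log of women eligible, invited and consented per clinician, and report it by staff group. If the full protocol already has such a rule, one sentence in the article would settle the matter.

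The cost is slightly slower recruitment and a little administration at the sites. No extra women are needed, and treatment and outcome measurement do not change. The log also lets readers judge whether uptake differed between staff groups. It does not make the comparison of delivery models a randomised one, and the report should continue to describe that comparison as exploratory.

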### Sample size

We have assumed that the minimum clinically important difference in the POP − SS is 2 [16] and that the standard deviation of the differences in POP − SS between baseline and one year will be 5.5 (as observed in POPPY). A sample size of 120 paired observations (with 2-sided alpha = 0.05) will therefore provide 80% power to detect important differences in POP − SS between baseline and one year.

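### Women are nested in about 24 clinicians, but the planned tests and models name no clinician-level clustering; at an assumed ICC of 0.01 to 0.10 the paired t-test's type I error would be about 5.5% to 10%

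*Protocol article*

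**What the plan says.** All references are to the protocol article.

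- **Grouping.** Data collection, B) Outcomes study: "It is anticipated that each staff member in the five sites will recruit five women to take part in the study". Recruitment/sampling: "We aim to recruit 120 women to the outcomes study". The outcomes study runs at five sites.
- **Role of the clinician.** The section on the PFMT intervention has the therapist assess the muscles, confirm technique, set and progress the home programme, and judge whether more or fewer appointments are needed. The first study aim in the Background is to explore whether different staff skill mixes can deliver PFMT without loss of clinical outcome.
- **Analysis.** Data analysis, B) Outcomes data: "We will initially examine the differences before and after intervention using paired t-tests and chi-square tests". Generalised linear models on the before-after difference follow, "adjusting for baseline measurements and potential confounders (e.g. demographic factors, study site" being the covariates described. No random effect, generalised estimating equation, cluster-robust variance or clinician term is mentioned.
- **Sample size.** "A sample size of 120 paired observations (with 2-sided alpha = 0.05) will therefore provide 80% power". The inputs are a 2-point difference and a standard deviation of 5.5 for the paired differences. No ICC or design effect is given.

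**The concern.** A paired t-test removes the correlation between a woman's two measurements, but it still treats the 120 differences as independent of each other. Here they come in groups of about five, each group handled by one clinician who tailors the treatment. The study deliberately varies who that clinician is. If outcomes depend at all on who delivers PFMT, women of the same clinician will have changes that resemble each other, and 120 women carry less information than 120 independent observations.

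Two results would be affected: the confidence interval and p-value for the overall POP-SS change, and any contrast between staff groups or delivery models. Staff group is a property of the clinician, so a term for site leaves clinician-to-clinician variation within site in the error. The economic evaluation may inherit the problem, because it is to use similar statistical models where appropriate.

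**Working it through.** **Inputs from the article.** Difference δ = 2, SD of differences = 5.5, N = 120, two-sided α = 0.05, five women per clinician (m = 5), five sites. Number of clinicians: 120 / 5 = 24.

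**Assumed input.** Clinician ICC for change in POP-SS. The article gives none. The range used is 0.01 to 0.10, with 0 as reference.

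**Step 1: the plan's own figure.** Pairs needed for 80% power: (5.5 × (1.960 + 0.842) / 2)² = 59.4, so 60 (62 with the t distribution). Power at 120 pairs: Φ(2 × √120 / 5.5 − 1.96) = Φ(2.02) = 97.8% (97.7% with t). The stated 80% is not reproduced. That is a separate point, but it shows how much room there is for a design effect.

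**Step 2: effect of clustering on the overall change.**

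- Design effect: DE = 1 + (m − 1) × ICC = 1 + 4 × ICC.
- Half-width ignoring clustering: 1.96 × 5.5 / √120 = 0.98. With clustering it is multiplied by √DE.
- True type I error of the ordinary test: 2 × (1 − Φ(1.96 / √DE)).
- Power at N = 120: Φ(2 × √(120 / DE) / 5.5 − 1.96), and the same with a t distribution on 23 degrees of freedom.
- N for 80% power: 59.4 × DE, rounded up.

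| ICC (assumed) | DE | √DE | 95% half-width (points) | Type I error | Power, normal / t | N for 80% power |
|---|---|---|---|---|---|---|
| 0 | 1.00 | 1.00 | 0.98 | 5.0% | 97.8% / 96.8% | 60 |
| 0.01 | 1.04 | 1.02 | 1.00 | 5.5% | 97.4% / 96.2% | 62 |
| 0.02 | 1.08 | 1.04 | 1.02 | 5.9% | 97.0% / 95.6% | 65 |
| 0.05 | 1.20 | 1.10 | 1.08 | 7.4% | 95.3% / 93.6% | 72 |
| 0.10 | 1.40 | 1.18 | 1.16 | 9.8% | 92.0% / 89.7% | 84 |

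**Step 3: check by simulation.** With 24 clinicians of five women each and no true change (20,000 runs per ICC), the ordinary paired t-test rejected 5.0%, 5.5%, 7.2% and 9.5% of the time at ICC 0, 0.01, 0.05 and 0.10. A t-test on the 24 clinician means rejected between 4.6% and 5.0%.

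**Step 4: does adjusting for site remove it?** A staff-group contrast was simulated with site as a fixed effect and two staff groups in each site. An ordinary linear model rejected a true null 6.0%, 7.4% and 10.1% of the time at ICC 0.02, 0.05 and 0.10. The inflation is about the same as for the overall change, so the site term does not cure it.

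The power figures assume that all 120 women provide both measurements. Steps 2 to 4 assume five women for every clinician; unequal caseloads would raise the design effect.

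**The case against.** **The inflation is conditional.** A reader might infer that the intervals are certainly too narrow and the error rate certainly above 5%. The article does not support that. It gives no ICC; at 0 nothing is lost, and at 0.01 the error rate is only 5.5%. This part of the objection stands in full.

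**The models are not closed.** A reader might infer that the generalised linear models definitely treat the women as independent. The article says only that appropriate models will be fitted, with an open list of example covariates, and the full analysis plan is not shown. A clinician term could be there. This stands for the models. It does not stand for the paired t-tests, chi-square tests and sample size, which are specific choices that assume independent women.

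**Site could be counted as a second random level.** That would give much larger error rates. But the three Realist Evaluation sites were chosen to reflect a deliberate mix, five sites are too few to estimate a site variance well, and the fix below treats site as fixed. Error rates that assume random sites are therefore not used here.

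**Staff-group contrasts might seem worse affected than the overall change.** Step 4 shows similar inflation, not more. The article also presents skill mix as something to explore and states no formal staff-group test.

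**The practical effect is modest.** At ICC 0.10 the half-width grows by 0.18 points (1.16 − 0.98), against an important difference of 2. This stands. A reader should not conclude that clustering leaves the study too small, or that it would by itself create a false claim that PFMT works.

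**Five per staff member is an expectation, and the article says recruit, not treat.** That is true. That the recruiting clinician also treats is a reasonable inference from the training section, but it is not stated.

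**Conclusion.** The concern holds in a limited form. The article describes a structure of about 24 clinicians with about five women each, makes clinician skill part of the question, and names tests that assume independence, with no clinician-level term. Across an assumed ICC of 0.01 to 0.10, standard errors are too small by a factor of 1.02 to 1.18 and the nominal 5% error rate becomes about 5.5% to 10%, both for the overall change and, at similar size, for staff-group contrasts adjusted for site. Clustering does not threaten the sample size: at ICC 0.10, 84 complete pairs would give 80% power by the normal approximation.

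The conclusion rests on three assumptions: the clinician ICC is above zero, the recruiting clinician delivers the treatment, and the results are meant to apply beyond these particular clinicians. The last fits the article's stated interest in knowledge that is useful for other settings. The results would remain usable without the change, but the intervals and any statement about who can deliver PFMT would probably be somewhat overconfident.

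**What to change.** 1. Link each woman's outcome data to the ID of the clinician who treats her. Intervention therapists already record appointment-level details for the costing, so this may need only a linking field.
2. Make the main POP-SS analysis a linear mixed model of the change, with a random clinician effect, site as a fixed effect and adjustment for baseline. The alternative is clinician-clustered standard errors with a small-sample correction, since there are only about 24 clusters. Keep the paired t-test as a descriptive first look.
3. Use the same error structure for any staff-group or delivery-model contrast, including effects and costs in the economic models where these are used.
4. Report the clinician ICC with its interval. It also describes how far outcome depends on who delivers PFMT, which the study sets out to learn.
5. If the full analysis plan already contains such a term, say so in the article's analysis section.

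The cost is a few sentences in the analysis plan, one linked field and slightly wider intervals: 1.08 instead of 0.98 points at ICC 0.05. No extra recruitment is needed on account of clustering.
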